### Informed consent

Prior to attending the physical examination screening a participant information sheet and consent form will be provided by post. The physiotherapist will offer an overview of the information sheet and answer any questions at the time of the initial telephone call. The potential participants will then be offered an appointment for a physical examination screening or, if more time is needed, will be offered a follow-up telephone call within the proceeding 2 weeks. If the participant does not wish to be considered for the study they will be thanked for their time and told that their referral will continue to be treated as per usual arrangements.

The potential participants will provide a signed consent form prior to the physical examination screening tests. Where consent is gained, the participants General Practitioner will also be informed of their inclusion in the study by letter. All potential participants who meet the criteria following physical examination screening will be eligible to be randomised. Those participants who do not meet the criteria will not be eligible to be randomised and will be informed of this along with the reasons. We expect only a small minority to be excluded at this stage and this aspect of the process is made clear in the information sheet.

### Baseline/outcome assessment

After the participants have been assessed for eligibility and consent has been gained, prior to randomisation, they will complete a range of appropriate patient-reported outcome measures to establish baseline pain, function, quality of life and level of self-efficacy. Additionally, the participants’ preference for one treatment or the other, if they had a free choice, will be noted to enable analysis of the effect of preference on outcome.

The primary aim of the proposed study is to evaluate the clinical and cost-effectiveness of self-managed loaded exercise versus usual physiotherapy for rotator cuff disorders. The primary outcome measure will be the Shoulder Pain & Disability Index (SPADI) [24] score at 12 weeks. SPADI is a self-report measure specifically developed to evaluate pain and function in patients with shoulder pathology [25]. It is a commonly used measure which has been validated for use in this patient population and a minimally clinically important change of 10 points has been identified [25]. The SPADI includes 13 items divided into 2 sub-scales; pain (5 items), disability (8 items). The responses are indicated on a visual analogue scale where 0 = no pain/no difficulty and 10 = worst imaginable pain/so difficult it requires help. The items are summed and converted to a total score out of 100.

The Short-form 36 (SF-36) is a generic measure of health related quality of life [26] and is the most widely used measure of this nature. The SPADI & SF-36 will be repeated at 12, 24 and 52 weeks and returned by post. These measures will be complemented by the patient specific functional scale (PSFS) which is a patient-specific outcome measure which investigates functional status and is intended to complement the findings of generic or condition-specific measures [27]. The PSFS has been shown to be valid and responsive in various musculoskeletal populations [28]. Due to the nature of the PSFS, this measure will be completed at baseline and then completed, until the end of the treatment episode, in the presence of the attending physiotherapist. Treatment duration is likely to be in the region of 3 months with the PSFS being completed at 1, 2 and 3 months post baseline.

We are interested in evaluating levels of adherence with treatment but also exploring possible factors that might predict non-adherence in this context. A range of such factors have been identified including level of pain at baseline, levels of physical functioning, levels of well-being [29], all of which can be captured with the aforementioned measures. However, levels of self-efficacy appear to be an important determinant of adherence [29] and so this will be captured via the General Self-efficacy scale (GSES) [30] at baseline. The GSES is a 10-item measure that has been developed to measure this construct and has been validated across different populations in different countries [31].

Due to the widely recognised limitations of clinical measures including range of movement and strength [32] these measures will not be undertaken as part of this study. In the absence of objectives measures of adherence, levels of treatment adherence will be formally measured through the use of an exercise diary including number and percentage of treatment sessions attended and percentage of exercises completed as reported by the patient.

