## Methods/Design

### Aims

The proposed study aims to answer the question: Is a self-managed exercise programme more effective than usual physiotherapy for chronic rotator cuff disorders?

The objectives are:

· To evaluate clinical effectiveness of loaded exercise in terms of pain, function and well-being.

· To evaluate cost-effectiveness of the interventions.

· To investigate patient adherence with treatment.

· To explore the perceptions and experience of the study participants.

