### The comparator

Usual physiotherapy might include a range of interventions including advice, stretching, exercise, manual therapy, massage, strapping, acupuncture, electrotherapy, corticosteroid injection at the discretion of the treating physiotherapist.

Prior to the recruitment of patients into the trial, the physiotherapists of Doncaster & Bassetlaw Hospitals NHS Foundation Trust who usually treat patients with rotator cuff disorders will be invited to participate in the study. A participant information sheet will be provided and explained via an initial information session delivered by the research team. If they wish to be included they will be asked to complete a consent form and return to the chief investigator within 2 weeks. During these training sessions the issue of contamination of the control arm and the implications will be discussed in an attempt to minimise contamination. The degree of any contamination will be evaluated via review of patient records and reported accordingly.

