### Economic analysis

A cost-utility analysis will be undertaken using a NHS and Personal Social Services (PSS) perspective. The health outcomes will be expressed in terms of quality adjusted life years (QALYs). The QALY combines length and quality of life into a single index number between 0 and 1 where 0 corresponds to a health state judged to be equivalent to death and 1 corresponds to optimal health. The SF-6D will be used to calculate QALYs. The SF-6D is composed of six multi-level dimensions which describes 18,000 health states in all. The SF-6D will be derived from a selection of SF-36 items which will be completed at baseline and follow-up visits during the trial. Any patient who completes the SF-36 can be uniquely classified according to the SF-6D.

Data regarding resource utilisation will be collected via patient notes and patient questionnaire returned at 3, 6 and 12 months along with the other measures of clinical outcome. A range of costs will be considered including the number of physiotherapy sessions attended, medications (including steroid injections) and referrals to surgery (with associated follow-up). These and other unit costs will be taken from the most recent National Reference Costs, British National Formulary and PSSRU publication ‘Unit costs of health and social care’. This will enable an estimation of the total cost for each participant as well as the average total cost for each treatment group.

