### Recruitment

Participants for the qualitative aspect of the study will be purposively selected from the treating physiotherapists and those patients recruited to the intervention arm of the RCT. All patient participants randomised to the intervention arm of the RCT will be eligible to enter and will be selected to gain a balanced sample of male/female and treatment adherers/non-adherers. All therapists involved in the delivery of the intervention will be eligible to enter.

Information relating to this aspect of the study will be included in the initial participant information sheet. The chief investigator (CL) will identify potential patient participants from the data generated by the RCT and will initially contact them by telephone to discuss whether they would be able to discuss their experiences. If their response is favourable then a separate consent form will be posted to them and completed prior to being invited to attend an individual interview at their convenience. The interviews may be conducted at the patients’ home or physiotherapy department.

The eligible physiotherapists will be approached as a group during the regular training sessions held throughout the duration of the trial, led by the chief investigator, and an open letter including a participant information sheet and consent form will invite them to contact CL with a view to discussing participation in this aspect of the study. If the physiotherapist wishes to participate then a mutually convenient individual interview at the physiotherapy department will be scheduled.

It is expected that interviews will last between 30 to 60 minutes. Purposive sampling will continue until data saturation. Data saturation is the point where on-going analysis reveals no new themes emerging from the data but it is estimated that 10 to 20 patient interviews will be required and up to 10 therapist interviews. Once it is thought that data saturation has been attained, 2 more interviews will be conducted to confirm this.

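### Clinic attendance is assigned to an exercise diary for want of objective measures, although the plan already uses patient notes, which are a better source for it

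*Protocol article*

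**What the plan says.** The Aims section of the protocol article lists among its objectives "To investigate patient adherence with treatment". The Baseline/outcome assessment section says how: "In the absence of objectives measures of adherence, levels of treatment adherence will be formally measured through the use of an exercise diary". The diary's stated content is "number and percentage of treatment sessions attended and percentage of exercises completed as reported by the patient". The same section wants to look for predictors of non-adherence and adds a self-efficacy scale at baseline for that purpose.

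Two other sections bear on the source of attendance data. Under Economic analysis, "Data regarding resource utilisation will be collected via patient notes and patient questionnaire returned at 3, 6 and 12 months", and "A range of costs will be considered including the number of physiotherapy sessions attended". The text does not say whether the notes or the questionnaire supplies the session count. Under The comparator, "The degree of any contamination will be evaluated via review of patient records and reported accordingly".

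The intervention section fixes no number of sessions: in both arms the treating physiotherapist decides how many, how often and when to stop. In the Recruitment section of the qualitative investigation, intervention-arm patients are "selected to gain a balanced sample of male/female and treatment adherers/non-adherers".

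**The concern.** Attending a clinic session and doing exercises at home are different things to measure. Nobody but the patient sees the home exercise, so a diary is a reasonable source for it. A clinic session takes place with NHS staff and would ordinarily leave a trace in the clinical record, which the trial already plans to consult. Giving the lack of objective measures as the reason for putting attendance in the diary therefore fits poorly with the rest of the plan. It also leaves two possible counts of the same quantity, one for adherence and one for costs, with nothing to link them.

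The adherence objective and the search for predictors of non-adherence are at stake, and to a lesser degree the choice of interviewees. All three need non-adherers to be identifiable. A source that depends on patients keeping and returning a diary may lose some of them.

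**Working it through.** **1. Sources side by side**

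| Section | Quantity | Source named |
|---|---|---|
| Baseline/outcome assessment | Sessions attended (count and percentage) | Exercise diary |
| Baseline/outcome assessment | Exercises completed (percentage) | Exercise diary, patient-reported |
| Economic analysis | Sessions attended (count) | Notes and questionnaire together, not split by item |
| The comparator | Contamination | Patient records |

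The trial therefore already consults the clinical record for two purposes and needs a session count for one of them. The lack of an objective measure is a sound premise for the second row and a poor one for the first.

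**2. The percentage**

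Percentage attended = sessions attended / sessions offered or booked. Because no number of sessions is fixed, the denominator differs from patient to patient and must be recorded for each. An exercise diary is a poor place to look for it, and clinic notes are the natural one. The Economic analysis section mentions only the numerator, so the denominator would be an extra item to extract.

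**3. Possible size of the effect**

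The document says nothing about diary return or levels of attendance, so every input here except N is an assumption.

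- N = 2 × 105 = 210 (Sample size calculation section).
- Assumed: 40% non-adherers attending 50% of sessions and 60% adherers attending 90%.
- True mean attendance = 0.4 × 50 + 0.6 × 90 = 74%.
- Assumed diary return: 90% in adherers. In non-adherers, r runs from 90% (equal return) through the midpoint (60 + 90)/2 = 75% to 60%.

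Formulas:

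- Share of diaries returned: R = 0.4r + 0.6 × 0.9
- Apparent non-adherence: 0.4r / R
- Apparent mean attendance: (0.4r × 50 + 0.54 × 90) / R

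| r | R | Diaries of 210 | No diary | Apparent non-adherence | Apparent mean attendance |
|---|---|---|---|---|---|
| 90% | 0.36 + 0.54 = 0.90 | 189 | 21 | 0.36/0.90 = 40% | (18 + 48.6)/0.90 = 74% |
| 75% | 0.30 + 0.54 = 0.84 | 176 | 34 | 0.30/0.84 = 36% | (15 + 48.6)/0.84 = 76% |
| 60% | 0.24 + 0.54 = 0.78 | 164 | 46 | 0.24/0.78 = 31% | (12 + 48.6)/0.78 = 78% |

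On these assumptions the bias runs from nothing to 9 percentage points in the share of non-adherers (40 − 31), and to 4 points in mean attendance (78 − 74). Some patients are lost in every row.

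**4. What does not change**

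The planned sample size reproduces. A difference of 10 points, SD 24, 80% power and two-sided 5% give 91 per group by the normal approximation. The source of attendance data enters neither this figure nor the primary SPADI comparison.

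**The case against.** The strongest reply is that this is loose wording in a condensed article. The phrase about patient report may attach only to exercises completed, and nothing forbids checking attendance against the notes. Using one count for costs and another for adherence is not in itself an error, and which one prevails could be left to a fuller document. This has some force, but it does not remove the point. The article names a source for attendance, gives a reason for the choice, and the reason does not suit that item. That is a stated choice which can be improved, not a missing detail.

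Several stronger readings are tempting, and the documents do not support them:

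- A reader might infer that the plan already extracts attendance from the notes. The Economic analysis section names notes and questionnaire together and assigns no item to either, so notes are the likely source but not the stated one.
- A reader might infer that the diary will overstate adherence. That requires lower diary return among non-adherers, on which the document is silent.
- A reader might object that exercise completion cannot be compared between arms, since exercise is only one discretionary option in usual physiotherapy. The article announces no such comparison. What remains is that a completion percentage has no meaning for a patient who was prescribed no exercise.
- A reader might propose using attendance to classify patients who return no diary. In a largely self-managed programme, attending the clinic does not show that home exercise was done, and two definitions of adherence would be mixed.

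The effect on interview selection is also modest. It is a purposive sample of an estimated 10 to 20 patients, drawn from the trial's data generally and not tied to the diary.

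**Conclusion.** The point holds in a limited form. For clinic attendance, the stated ground for relying on the diary fits poorly with a plan that counts sessions for costing, names patient notes as a data source and reviews patient records. Clinic notes are the better source for attendance and for its denominator, on the ordinary assumption that they record sessions booked and attended.

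Any bias depends on differential diary return, and the figures above illustrate it without estimating it. The loss of patients without a diary needs no such assumption, only that some diaries do not come back. The point reaches a non-primary objective only, and is a worthwhile refinement, not a serious fault.

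**What to change.** In the Baseline/outcome assessment section, state that attendance is taken from the clinic notes for all randomised patients, as a number and as a percentage of the sessions offered or booked for that patient. State in the Economic analysis section that the same count is used for costing.

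Keep the diary for home-exercise completion, described among patients who were prescribed exercise. Report attendance and exercise completion as two separate measures, and do not let attendance stand in for home-exercise adherence where no diary is returned.

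The cost is a sentence or two of text and one further item, sessions offered or booked, to extract from notes that the plan already uses.

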### Randomisation

Block randomisation will be carried out by an administrator based in the physiotherapy department but independent to the study. Following receipt of written informed consent and baseline assessment, a computer generated random number sequence indicating group allocation will be concealed in sealed opaque envelopes which will be consecutively numbered. The group allocation and baseline PSFS assessment will be attached to the patient referral for the attention of the treating physiotherapist in readiness for the programme of treatment.

### Sample size calculation

The sample size calculation is based upon the primary outcome measure, the SPADI, where a 10-point change is regarded as a minimally clinically important change in shoulder function [24]. Assuming a standard deviation of 24 points, a power of 80% and a (two-sided) significance level of 5%, 91 participants per group will be required. We will allow for a 15% loss to follow-up and aim to recruit 105 participants per group. Data from the Physiotherapy department at Doncaster & Bassetlaw Hospitals NHS Foundation Trust indicates that 70 potentially suitable patients are referred for treatment each month. Hence a recruitment rate of 17 to 18 per month is felt to be realistic and manageable in the allotted timescale.

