**Methods/Design:**

A single-centre pragmatic unblinded parallel group randomised controlled trial will evaluate the effectiveness of a self-managed loaded exercise programme versus usual clinic based physiotherapy. A total of 210 study participants with a primary complaint of shoulder pain suggestive of a rotator cuff disorder will be recruited from NHS physiotherapy waiting lists and allocated to receive a programme of self-managed exercise or usual physiotherapy using a process of block randomisation with sealed opaque envelopes. Baseline assessment for shoulder pain, function and quality of life will be undertaken with the Shoulder Pain & Disability Index, the Patient Specific Functional Scale and the SF-36. Follow-up evaluations will be completed at 3, 6 and 12 months by postal questionnaire. Both interventions will be delivered by NHS Physiotherapist’s.

An economic analysis will be conducted from an NHS and Personal Social Services perspective to evaluate cost-effectiveness and a qualitative investigation will be undertaken to develop greater understanding of the experience of undertaking or prescribing exercise as a self-managed therapy.

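### The recruitment target of 105 per group covers a loss of about 13%, not the stated 15%: a minor arithmetic slip that costs about 0.9 points of power

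*Protocol article*

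**What the plan says.** The section headed Sample size calculation gives these inputs for the primary outcome, the SPADI:

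- Difference to detect: "a 10-point change is regarded as a minimally clinically important change in shoulder function".
- Spread: "Assuming a standard deviation of 24 points".
- Error rates and result: "a power of 80% and a (two-sided) significance level of 5%, 91 participants per group will be required".
- Allowance for loss and target: "We will allow for a 15% loss to follow-up and aim to recruit 105 participants per group".

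The Methods/Design paragraph of the Abstract carries the target forward as a total: "A total of 210 study participants", which is 2 × 105. The formula used to get from 91 to 105 is not stated. The Data analysis section names an unadjusted two-sample t-test on the 12-week SPADI total as the primary comparison. Regression or ANCOVA comes in only if the groups differ at baseline.

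**The concern.** An allowance for loss should bring in enough people that the required number remains after the loss. If a fraction *L* of those recruited is lost, the target is the required number divided by (1 − *L*). Multiplying by (1 + *L*) always gives too few, because the loss then acts on the enlarged number and not on the original one. The step from 91 to 105 looks like such a multiplication.

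If so, the required number, the loss and the target cannot all be true together. Either the loss that the trial can bear is below 15%, or the number left for analysis is below the one the same paragraph calls necessary. At stake is the accuracy of the sample size justification, which the trial report will normally repeat and which any reader can check in one line.

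**Working it through.** **Inputs** (all from Sample size calculation, except the total, which is in the Abstract): difference δ = 10; SD σ = 24; power 80%; two-sided α = 0.05; 91 required per group; 15% loss; 105 recruited per group; 210 in total.

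**1. Reproduce the required number.** Normal approximation for two means:

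n = 2 (z₀.₉₇₅ + z₀.₈₀)² σ² / δ² = 2 × (1.96 + 0.8416)² × 24² / 10² = 90.42, rounded up to **91**.

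This is the plan's figure exactly.

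**2. Reproduce the target.**

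- Multiplication: 91 × 1.15 = 104.65, rounded up to **105**. This is the plan's figure.
- Division: 91 / 0.85 = 107.06, rounded up to **108** per group, 216 in total. (Inflating the total of 182 directly gives 182 / 0.85 = 214.12, that is 215.)

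Only the multiplication gives 105. That this route was used is an inference from the match. The next step does not depend on it.

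**3. Check the target against the stated loss.**

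- Expected to remain: 105 × 0.85 = 89.25 per group, or 210 × 0.85 = 178.5 in total, against 91 and 182.
- Largest loss that still leaves 91: 1 − 91/105 = 0.133, that is **13.3%**.

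**4. Cost in power.** Normal approximation: power = Φ(δ / (σ √(2/n)) − 1.96).

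- n = 91: 24 × √(2/91) = 3.558; 10 / 3.558 = 2.811; Φ(0.851) = 0.803.
- n = 89: 24 × √(2/89) = 3.598; 10 / 3.598 = 2.780; Φ(0.820) = 0.794.

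The t-test column below uses the noncentral t distribution.

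| Analysed per group | Normal approximation | t-test |
|---|---|---|
| 91 (required) | 80.3% | 79.8% |
| 89.25 (expected) | 79.5% | 79.1% |
| 89 (whole participants) | 79.4% | 78.9% |

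Going from 91 to 89 costs 0.9 points in either column. The difference detectable with 80% power at 89 per group is (1.96 + 0.8416) × 3.598 = 10.1 points, against the planned 10.

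**The case against.** The best reply is that nothing of consequence follows. The slip costs 0.9 points of power, while the SD of 24 is itself an assumption. With 89 per group and the t-test, power is 82.2% if the SD is 23 and 75.6% if it is 25. A change of one point in the SD therefore moves power by more than three points, several times the effect of the slip. The 15% is also a planning guess. This stands, and it sets the rank of the point. It does not make the figures agree.

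A second reply is that the 15% may have been meant as a proportion of the 91 completers. That reproduces 105, but it is not a loss rate among those recruited. Expressed as one, it is 13.3%.

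Three stronger readings are tempting, and the documents support none of them:

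- *That the trial is materially underpowered.* Power of about 79% in place of 80% does not bear this out.
- *That 91 is also wrong because the analysis is a t-test.* A t-based calculation gives 91.39, that is 92. But the article does not claim that method, the normal approximation is an accepted convention, and 91 reproduces exactly under it. Part of the gap between 78.9% and 80% comes from this convention: the full 91 already gives 79.8% under the t-test.
- *That adjustment for baseline SPADI makes good the shortfall.* The Data analysis section fixes no baseline-adjusted primary analysis; adjustment is conditional on baseline differences. The documents also give no correlation between baseline and 12-week scores from which a gain could be worked out.

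**Conclusion.** The sample size paragraph is wrong as written, and the error is minor. A target of 105 per group is not consistent with 91 required and 15% lost: about 89 remain, and the loss that can be borne is 13.3%. The shortfall against a target obtained by division is 3 per group, 6 in total. Power is about 79% (79.4% normal approximation, 78.9% t-test), of which about 0.9 points is due to the slip.

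The inconsistency rests on the article's own figures alone. The power figures add three assumptions: the stated difference and SD hold, loss is equal in the two groups, and participants lost to follow-up contribute no 12-week score to the t-test. That the cause was multiplication by 1.15 is very likely from the exact match, but it is an inference.

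**What to change.** Keep 210 and correct the sentence on loss, for example: *A target of 105 per group allows for about 13% loss to follow-up; with 15% loss about 89 per group remain, giving about 79% power for the unadjusted t-test.*

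This is a change of wording only. Its one cost is a stated power slightly below 80% under the 15% scenario.

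If the sponsor prefers to keep both 15% and 91, the matching target is 108 per group, 216 in total, and the total in the Abstract changes with it. At the recruitment rate of 17 to 18 per month given in the same section, six more participants take about a third of a month (6 / 17.5 = 0.34). For a gain of this size the wording change is enough.
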